## **5. Methods:**

### **Study design:**

#### **Working plan A (WPA):**

#### **Cardiometabolic phenotyping:**

To address aim 1 we will perform a cross-sectional study in patients, who are in routine care at the endocrine outpatients' clinic for the hormonal work up of an adrenal adenoma. 25 patients with an ACS will be recruited and compared to 25 patients of comparable age and sex with a sufficient suppression of cortisol  $< 1.8$  ug/dl following a 1 mg dexamethasone suppression test.

Experiments will be performed in the morning after an overnight fast. Subjects have to avoid intense physical exercise and consumption of alcoholic beverages for at least 48 hours previous to study related experiments.

$^1\text{H}$  magnetic resonance (MR) spectroscopy measurements will be performed in high field 3T whole body MR system (Magnetom, Siemens Healthcare, Erlangen, Germany) equipped with appropriate surface coils. Ectopic fat in the liver, the skeletal muscle and the myocardium will be assessed by the single voxel localized  $^1\text{H}$  MRS method (41).

After the MR measurements a frequently sampled oral glucose tolerance test will be performed and surrogate parameters of insulin secretion and sensitivity will be

calculated based on validated indices (HOMA\_IR, CLIX, OGIS, IGI, Disposition Index, Adaptation Index) (21).

Additionally, blood will be drawn at baseline for the measurement of parameters of systemic inflammation (CRP, IL-6, PAI-1, TNF-alpha, homocysteine, leucocytes, monocytes), the renin-angiotensin-aldosterone system (RAAS FINGERPRINT ®) and hypercoagulability (TECHNOTHROMBIN ®).

To estimate diurnal cycles of cortisol secretion salivary cortisol will be drawn at 8:00 a.m. and midnight.

To address aim 2, additional blood will be drawn to analyze the peroxiredoxin oxidation cycles from red blood cells (19), as well as the circadian clock transcript changes from peripheral blood mononuclear cells (21).

In addition, blood will be stored for combined untargeted/targeted LC-MS/MS based metabolomic/proteomic approaches.

Overall, 125 ml blood will be drawn in total for all biochemical analyses of WPA.

A systematical assessment of the chronotype will be performed by using the Munich ChronoType Questionnaire. Furthermore, the following psychological tests will be applied:

- Measurement of vigilant attention and impulsivity (by means of the Psychomotor Vigilance Task)
- Implicit association of concepts (by the Implicit Association Test)

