### **Statistical Analysis:**

Data will be presented as means  $\pm$  SD or median (minimum; maximum) depending on normal distribution. Normal distribution will be checked by data visualization and the Kolmogorov-Smirnov test.

Due to the exploratory design of the study, there will be no correction for multiple testing. Due to the exploratory design of the study, there will be no correction for multiple testing.

Hepatic lipid content (HCL) will be considered as primary outcome parameter.

Nullhypothesis: There is no difference in HCL between patients with ACS and the control group.

Alternative hypothesis: There is a difference in HCL between patients with ACS and the control group.

Aim 1: comparisons between the groups of patients with ACS and the control group without ACS will be performed by unpaired student's t-tests. In case of a large distribution of age between the groups, an adjustment by a regression model will be performed.

Aim 2: Comparisons of metric variables between the groups of patients will be performed by unpaired student's t-tests or Mann-Whitney-U tests, depending on normal distribution. Chi-squared test will be used for comparison of discrete variables.

Aim 3: longitudinal analysis before and after treatment will be performed by using paired student's t-tests.

Associations between continuous variables will be described by Pearson's correlation coefficient.

SPSS - Statistics will be used for all computations. Level of statistical significance is set at  $p < 0.05$ .

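### Age adjustment of the primary hepatic lipid comparison is left to an undefined, data-driven trigger and sex is not adjusted for; one fixed model with age and sex should replace it

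*Protocol*

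**What the plan says.** Protocol section 14, Statistical Analysis, names the outcome: "Hepatic lipid content (HCL) will be considered as primary outcome parameter". For Aim 1 it states that "comparisons between the groups of patients with ACS and the control group without ACS will be performed by unpaired student's t-tests", followed by the only provision for covariates: "In case of a large distribution of age between the groups, an adjustment by a regression model will be performed". No cut-off for *large* is given, and age is the only covariate named. The text does not say whether the regression replaces the t-test or stands beside it.

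Section 5, Working plan A, describes how the comparison group is formed: "25 patients with an ACS will be recruited and compared to 25 patients of comparable age and sex". No matching procedure or tolerance follows, and the control inclusion criteria under Patients' population ask only for adult age, an adrenal adenoma and a suppressed cortisol.

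**The concern.** The two groups are not randomised, so the primary estimate depends on how well they are balanced and on what the model does about the remainder. The plan treats age and sex as important enough to select on. It then leaves sex out of the analysis and brings age in only if the observed imbalance looks large to the analyst.

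Two things follow. First, an age imbalance too small to trigger the adjustment passes into the primary estimate. Second, because the trigger is undefined, two analyses of the same data could each be defended as the planned one, and the choice would be made after the data are seen. The primary p-value then has no single pre-specified meaning.

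**Working it through.** **Inputs from the Protocol** (section 14, Sample size calculation and Statistical Analysis): 25 per group; control HCL 5 ± 2.5; expected difference 25%, that is 0.25 × 5 = 1.25 points; two-sided test at 0.05 (the alternative hypothesis has no direction).

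**Assumptions, not in the Protocol:** age-HCL correlation ρ of 0.3 to 0.5; true age gap δ of 0, 0.3 or 0.5 SD; two readings of *large*, namely a significant age t-test (p<0.05) or an observed gap above 0.3 SD. HCL is taken as normal with within-group SD 2.5. Results in steps 3 to 6 come from simulation (40,000 trials per cell).

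**1. The plan's own figure.** n = 2 × (1.96 + 0.84)² × (2.5/1.25)² ≈ 63 per group (64 with the t distribution), against the stated 25. Power with 25 per group is about 41%. The stated size is not reproduced. That is a separate issue, and 41% serves here only as the reference for step 6.

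**2. Bias with no adjustment.** Bias = ρ × δ × 2.5. The extremes are 0.3 × 0.3 × 2.5 = 0.225 and 0.5 × 0.5 × 2.5 = 0.625 points.

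**3. How often the trigger fires.** With 25 per group, p<0.05 needs an observed gap above 2.011 × √(2/25) = 0.57 SD. It fires in about 18% of trials when δ = 0.3 and 41% when δ = 0.5. A 0.3 SD trigger fires in about 52% and 76%.

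**4. Average bias in HCL points.**

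| ρ | δ | Never adjust | p<0.05 trigger | p<0.05 trigger, trials where it does not fire | 0.3 SD trigger | Always adjust |
|---|---|---|---|---|---|---|
| 0.3 | 0.3 | 0.225 | 0.13 | 0.16 | 0.03 | 0 |
| 0.3 | 0.5 | 0.375 | 0.14 | 0.25 | 0.02 | 0 |
| 0.5 | 0.3 | 0.375 | 0.22 | 0.27 | 0.05 | 0 |
| 0.5 | 0.5 | 0.625 | 0.24 | 0.40 | 0.04 | 0 |
| either | 0 | 0 | 0 | 0 | 0 | 0 |

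As a share of the target: 0.02/1.25 ≈ 2% to 0.24/1.25 ≈ 19%.

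**5. False positives with no true HCL effect.** If the p<0.05 trigger is followed faithfully, the type I error at δ = 0.5 is 5.3% (ρ = 0.3) to 6.0% (ρ = 0.5). If the analyst is free to report either model, the chance that at least one gives p<0.05 is about 6 to 7% with no age gap, rising to about 16 to 17% at ρ = δ = 0.5. Much of that rise is bias in the unadjusted test, which on its own rejects in 13.9% of trials in that cell. The fixed adjusted model stays at about 5% throughout.

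**6. Power with no age gap and a true difference of 1.25.** The unadjusted test and the p<0.05 rule both give about 41%. Always including age gives 44% (ρ = 0.3) to 51% (ρ = 0.5). Sex was not simulated.

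**The case against.** - **Selection already deals with age and sex.** Controls are to be of comparable age and sex, so a true gap of 0.3 to 0.5 SD supposes that selection partly fails. This stands. A reader might infer that the plan leaves confounding in place; that is too strong. What remains is residual bias when the trigger does not fire, and none if there is no true gap. Yet no tolerance is given, and the conditional sentence itself foresees that balance in age may fail.
- **The size depends on an assumed trigger.** This also stands: a 0.3 SD reading leaves at most about 0.05 points, so the upper figures hold only for a significance trigger. That the result moves so much with the reading of one word is itself part of the problem.
- **A statistical analysis plan may define the trigger.** It may, and it may also say which result is primary. But the Protocol sentence already fixes a conditional rule, and a threshold would not make it unconditional or bring sex in.
- **The study is a pilot and exploratory.** True, and it limits the severity. It is no reason to leave the one named primary comparison open.

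A reader might also infer that the t-test on untransformed HCL loses power because the effect is stated in percent, or that the normality check ("Normal distribution will be checked by data visualization and the Kolmogorov-Smirnov test") is too weak to protect it. The documents do not support this. They give only a mean and SD, not a shape. At a coefficient of variation of 0.5, raw against log power with 25 per group is 34% against 37 to 38% for lognormal data, but 33% against 31% for gamma data and about 38 to 41% against 34% for near-normal data. The direction depends on the unknown shape, the raw t-test keeps its type I error in the lognormal case (4.7%), and values at or near zero would be awkward on the log scale. The same holds for the paired comparison in Aim 3, where any gain from logs rests on the same unstated shape.

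**Conclusion.** The point holds in limited form. The Protocol prescribes a data-triggered, age-only adjustment with no threshold for a non-randomised primary comparison, omits the other factor on which controls are selected, and does not say which of two possible results is primary.

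The existence of the defect can be read directly from the text. Its size cannot: 2 to 19% of the target difference rests on the assumed correlation, age gap and trigger, and the bias is zero if selection achieves true balance in age. The change is worth making because a fixed adjustment removes the age bias in every case examined, gives the p-value one meaning, and under the assumed correlations does not lose power. It does not bring 25 per group near 80% power.

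**What to change.** Replace the conditional sentence in section 14, Statistical Analysis, with a fixed primary analysis, for example: *HCL will be compared between groups by linear regression on group, age and sex; the adjusted mean difference with its 95% confidence interval is the primary result, whatever the observed balance in age. The unadjusted unpaired t-test is a sensitivity analysis.*

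A log-scale analysis of HCL may be added as an optional sensitivity analysis, with a stated rule for values at or near zero. It need not be primary. Insulin resistance and visceral fat should stay out of the primary model, because the sample-size section treats them as reasons for the higher HCL and they may lie on the causal path.

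The cost is two residual degrees of freedom (48 to 46) and a few sentences of text. Age and sex are already used to choose controls, the model runs in the software named, and the estimate stays a difference in HCL as in the stated hypotheses. The sample-size shortfall needs its own correction.
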